### Objectives

The aim of the trial is to evaluate the clinical effectiveness and implementation of the ACHRU-CPP, compared to usual care. We hypothesize that clients in the intervention group will experience greater improvements in health-related quality of life (HRQoL) compared to the usual care group. We also expect that the program will improve outcomes for family caregivers, improve interprofessional team functioning among the interventionists, and be feasible to implement in practice at no additional cost. The study will address the following specific objectives:To compare the effects of the intervention versus usual care on older adults’ HRQoL, diabetes self-management, self-efficacy, depressive symptoms, anxiety, and the costs of use of health services (from a societal perspective)To determine the subgroups of older adults that benefit most from the programTo compare the effects of the intervention versus usual care on family caregivers’ HRQoL, strain, depressive symptoms, and the costs of use of health services (from a societal perspective), andTo evaluate the implementation of the program and its effects on interprofessional/team collaboration

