*Feasibility*: the capability to carry out intervention activities	- Training of the interventionists - Delivery of the program - Perceptions of barriers and facilitators	- Evaluation of training materials, log sheets - Qualitative descriptive method to analyze focus group content
*Fidelity*: adherence to intervention components	Refer to Fidelity Checklist (Additional file 3)	- Review records of attendance at training session and monthly meetings with researchers - Review home visit records and log sheets to assess delivery of the program as planned
*Reach*: degree to which the target population is eligible to receive the intervention (coverage)	- Proportion of clients eligible - Reasons for exclusion - Characteristics of eligible clients	- Descriptive statistics
*Maintenance*: the extent to which the intervention can be sustained	- Engagement rate (%) - Attrition /retention (%) - Reported reasons for attrition - Prospects for the program’s uptake in practice setting	- Descriptive statistics - Qualitative descriptive method to analyze focus group content
*Cost*: from a societal perspective	- Health and Social Services Utilization Inventory (HSSUI) [90]	- Comparison of baseline (*T* _1_) and 6-month (*T* _2_) median costs using Mann-Whitney *U* test

Appropriateness and feasibility will be evaluated based on the results of the monthly outreach meetings and focus group sessions with interventionists. These meetings and focus group sessions will provide information on the perceived impact, and barriers and facilitators to implementation of the program. Questions asked during the focus group session will be guided by the CFIR [47] framework which facilitates the systematic exploration of the appropriateness and feasibility of the program in terms of barriers and facilitators. CFIR focuses on examining the following key domains: intervention characteristics (e.g., complexity of intervention, perception of benefits and relative advantage compared to usual practice), outer setting (e.g., credibility of intervention by provider and senior administrative agents), inner setting (e.g., team characteristics and engagement, level of coordination and collaboration, involvement of clients and caregivers, compatibility with existing systems and resources), and individuals (e.g., enthusiasm and support for intervention, consistent tracking of activities, reporting and resolving challenges, robust referrals).

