Costing will assume a societal perspective [89], which implies collecting all costs, regardless of who bears them. The wider the perspective taken, the more applicable the study is to social-policy decisions. The costs of use of all types of health services from baseline to 6 months in T2DM clients and their family caregivers will be determined using the Health and Social Services Utilization Inventory (HSSUI) [90]. The HSSUI consists of questions about the respondent’s use of the following direct health care services: (1) primary care, (2) emergency department and specialists, (3) hospital days, (4) other health and community support services, and (5) prescription medications. Services specific to the program will be captured such as interventionist training, delivery of services in group sessions and in-home visits, and attendance at case conferences and outreach visits. Inquiries are restricted to the reliable duration of recall: 6 months for remembering a hospitalization and a visit to the physician, and 2 days for use of a medication. The HSSUI builds on the work of Browne et al. [91, 92] whose work was tested and assessed for reliability and validity and was acknowledged as one of the few published measures of ambulatory utilization that is empirically validated [93]. The 6-month cost data will be derived from “quantity” data for the services identified in the HSSUI and current “price” data for each service [90]. Services include: physician costs, home care services, outpatient costs, X-rays, other health care providers, emergency services, medication costs, tests, emergency room and hospitalization, and caregiver support services [90]. The product of the number of units of service (quantity) and unit cost (price) is total cost.

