### Implementation analyses

Table 3 also provides the types of analyses that will be undertaken in the implementation evaluation. Both quantitative and qualitative methods will be employed in the evaluation, depending on the outcome being examined. Acceptability will be assessed by comparing observed rates (e.g., enrollment, eligibility, engagement, and dose) with preset targets. Many of these rates will also be used in evaluating maintenance. Reach will be assessed by reviewing baseline characteristics of the total sample and comparing these to the broader population of older adults with T2DM and MCC. A review of the records on eligible clients will also be conducted, to compare those that enroll in the study to those that do not enroll, withdraw or are lost. These records will capture demographic characteristics (e.g., age, gender, comorbidity, and site) as well as the reasons clients declined to participate, withdrew, or were lost. These analyses will enable us to assess the representativeness of the intervention group compared to those that were eligible but declined to participate, withdrew, or were lost. We will also examine the reasons for refusal and evaluate whether declines can be attributed to the nature of the program being offered.

Qualitative descriptive methods will be used to assess the content of focus groups, outreach meeting records, and other documents (e.g., log sheets documenting delivery of program components and principles used). Data from the focus groups will be digitally recorded and transcribed by an experienced transcriptionist and checked for accuracy by a RA. The data will be managed using N-Vivo 10 software. Content analysis will be used to analyze the transcripts. Two research investigators will independently review all transcripts and inductively generate a list of codes describing the content. The codes will then be grouped into themes (a higher conceptual level) and subthemes. Difference of opinion between the two investigators will be discussed until agreement is reached.

The cost analyses will involve comparing the cost of use of specific health and social services between the intervention and control groups. Because cost data are often right skewed, we anticipate using nonparametric tests (e.g., Mann-Whitney *U* test) to evaluate differences in median costs between the two groups. We will also estimate the costs of the program, and total costs of health care and social service in the two groups.

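### The Table 3 cost row conflicts with the text, and the only cost test named compares ranks, which cannot settle whether the program adds cost

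*Protocol article*

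**What the plan says.** **Expectation.** Under Objectives, the investigators expect the program to "be feasible to implement in practice at no additional cost". The Discussion adds that the cost analysis will tell policy-makers what the program means for resources.

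**Test in the text.** Under Implementation analyses: "Because cost data are often right skewed, we anticipate using nonparametric tests". Mann-Whitney is given as the example, "to evaluate differences in median costs between the two groups". The next sentence adds: "We will also estimate the costs of the program, and total costs of health care and social service in the two groups".

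**Test in Table 3, Cost row.** "Comparison of baseline (*T* _1_) and 6-month (*T* _2_) median costs using Mann-Whitney *U* test". The row does not mention study arms.

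**General rule.** Under Analysis of participants, all tests are two-sided at 0.05. No cost margin is given anywhere.

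**Perspective.** Under Analysis of implementation, Outcomes: "Costing will assume a societal perspective [89], which implies collecting all costs, regardless of who bears them". The inventory is then described as asking about "use of the following direct health care services", in five groups that include community support services. Program-specific costs are captured as well, and a further list includes home care and caregiver support services.

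**The concern.** Three things do not fit together.

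1. Table 3 and the text assign one test to two different contrasts. Baseline and 6-month costs come from the same clients, so an independent-samples test is wrong for the row as written.
2. What a program costs a payer is the number of clients times the mean cost. Mann-Whitney responds to rank order, and it is a test of medians only when the two distributions differ by a shift. With skewed costs it can miss a rise in mean cost that comes from a few expensive clients, and it can signal a difference when mean costs are equal.
3. An expectation of no added cost is a claim about the absence of an increase. A non-significant two-sided test does not establish it.

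At stake is what the cost result can tell policy-makers, which the Discussion presents as one of the study's main contributions.

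**Working it through.** **Sample size for the checks.** The plan's own figure reproduces. Effect size 0.50, two-sided 5% and 80% power give n = 2(1.96 + 0.8416)²/0.50² = 62.8, so 63 per arm, or 64 with the t distribution. Dividing 64 by 0.80 for attrition gives 80 per arm, as stated. I therefore use 64 completers per arm. The abstract gives 160 participants in total, while Participants and setting gives 160 in each province; pooling 320 would double the completers to 128 per arm. The protocol gives no cost SD or margin, so every cost spread, correlation and margin below is an assumption.

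**1. Table 3 row taken literally.** Unpaired Mann-Whitney was applied to paired lognormal costs (log-SD 1, 64 clients, 5,000 simulated trials).

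| Within-person correlation | Type I error at nominal 5% |
|---|---|
| 0.3 | 2.0% |
| 0.5 | 0.7% |
| 0.7 | 0.1% |

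At correlation 0.5, power for a 30% rise is 23%, against 53% for the signed-rank test.

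**2. Equal medians, different means.** Lognormal mean = median × exp(s²/2). Take a median of 2,000 in both arms and log-SD 1.0 against 1.25:
- means: 2,000 × exp(0.5) = 3,297 and 2,000 × exp(0.78125) = 4,368
- difference 1,071; ratio exp(0.28125) = 1.32, or 32% higher
- Mann-Whitney rejects in about 5% of trials, the null rate
- a Welch test on means rejects in about 12%

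Other spreads agree. With mean cost 25%, 49% or 62% higher, Mann-Whitney rejects in 5.0%, 5.4% or 5.3% of trials.

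**3. Equal means, different medians.** With median ratios of 0.80, 0.67 and 0.62 and identical mean cost, Mann-Whitney rejects in 20%, 57% and 58% of trials.

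**4. What non-significance shows.** If every intervention-arm cost were 20% higher, p would be 0.05 or more in 76%, 83% and 90% of trials at log-SD 0.8, 1.0 and 1.5. With 128 per arm the figures are 57%, 72% and 84%.

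**5. What an interval on the mean would look like.** 95% half-width as a share of the mean = 1.96 × CV × √(2/64) = 0.3465 × CV. That gives 35%, 52% and 69% at CV 1.0, 1.5 and 2.0. With 128 per arm, dividing by √2 gives 24%, 37% and 49%. Showing that mean cost rises by no more than 20% (one-sided 0.025, 80% power, true difference zero) would need 393, 883 or 1,570 per arm at those CVs.

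**6. Perspective, by reading.** The definition covers all costs. The items named are health, community and caregiver support services and program delivery. Productivity loss and unpaid care time are not named.

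**The case against.** The strongest case against has four parts.

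- **Table 3 is probably condensed wording.** The abstract and Implementation analyses make the between-arm intent clear, and the row could mean that arms are compared at each time. That is a fair guess at the intent, but the row does not say so, and the conflict lies within this document.
- **The text is tentative and continues.** A reader who stops at the Mann-Whitney sentence might infer that total cost is ignored. It is not: program cost and total cost in the two groups are to be estimated, and results of all models are promised with effects and 95% intervals. That stands and softens the point. However, no between-arm difference or interval is tied to the totals, and the one comparison named for testing is on ranks.
- **No decision rule is stated.** A reader might infer that p > 0.05 will be reported as no additional cost. Nothing in the article says that; the Objectives state an expectation. What remains is that the named test could not confirm that expectation.
- **The remedy is not more powerful in any useful sense.** In the example in step 2, the Welch test rejects in only 12% of trials. The SDs are 3,297 × √(e − 1) = 4,322 and 4,368 × √(e^1.5625 − 1) = 8,482, so the standard error is √((4,322² + 8,482²)/64) = 1,190 and the half-width about 2,330, against a true difference of 1,071. This stands. The case for the mean is that it is the right quantity, reported with honest uncertainty. A pre-set margin would usually be inconclusive at this size.

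On perspective, a reader might infer that the choice of test undermines the societal claim, or that out-of-pocket costs are left out. Neither follows. A test has no bearing on which costs are collected, and the list prices services used without saying who pays. The full inventory may also hold more than the article lists. The choice of cost model is normally left to an analysis plan, and its absence here is not held against the article.

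**Conclusion.** The concern holds in a limited form. The Table 3 row is wrong as written and conflicts with the text. The only inferential cost comparison named addresses ranks or medians, while the expectation of no added cost and the stated use for policy depend on mean total cost. In the assumed example, a 32% higher mean cost goes undetected beyond the null rate. If all costs truly rose by 20%, a non-significant result would still occur in 76% to 90% of trials at 64 per arm. These sizes rest on assumed lognormal costs and log-SDs. The direction does not depend on the exact values, and it is unchanged at 128 per arm.

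The point is worth correcting but secondary: cost is not the primary outcome, the choice of test is tentative, and total costs are to be estimated anyway. The perspective label is a separate and more minor matter.

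**What to change.** 1. Correct the Cost row of Table 3 to a between-arm comparison, in line with Implementation analyses.
2. State that the main cost result is the between-arm difference in mean 6-month total cost per client, including program cost, with a 95% CI (for example by bootstrap or a gamma GLM, adjusted for baseline cost and site). Keep Mann-Whitney as descriptive.
3. Treat the expectation of no additional cost as something to be judged from that estimate and interval, not from p > 0.05.
4. Describe the perspective as health and social service costs wherever it is called societal, unless the inventory also collects productivity loss and unpaid care time.

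The cost is a few lines of wording and minor programming, with no new data. The price is a wide interval and a cost conclusion that will often be inconclusive, which the article should say in advance.

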## Discussion

This paper describes the design of a multisite, two-arm, pragmatic, mixed-methods RCT of the effectiveness of the ACHRU-CPP aimed at improving self-management in older adults with T2DM and MCC and providing support to caregivers. This research makes several important contributions to the existing knowledge base. First, it investigates the effectiveness of a self-management intervention in a complex population. This population is particularly at risk of adverse outcomes, yet they are often excluded from RCTs. As a result, their needs are poorly understood and evidence of the effectiveness of interventions aimed at behavioral change in this vulnerable group is lacking. The exclusion of this group is important; about 60% of older adults with T2DM have at least one comorbid condition and 40% have three or more [8–10]. Second, the study includes a subgroup analysis to determine which study clients benefit most from the program. Few intervention studies conduct this type of analysis, yet it is critical for informing the implementation of the program in other settings and to target scarce resources to those most likely to benefit [86]. Third, the study includes a cost analysis, which provides policy-makers with critical information on the resource implications of the program to facilitate decision-making.

There are several strengths of the design of this study. First, the intervention being evaluated targets behavioral change, consistent with the epidemiological roots of T2DM and supported by behavioral theory and empirical results demonstrating the effectiveness, sustainability and scalability of self-management interventions for T2DM. Second, the study combines effectiveness and implementation research, which is consistent with a comprehensive approach to evaluation and offers the potential to reduce the research-to-practice gap [42]. With equal weighting assigned to both implementation and effectiveness, our study best fits the type-2 hybrid effectiveness-implementation study design using the typology proposed by Curran et al. [42]. These researchers argue that hybrid designs offer the potential to accelerate the translation of research into routine practice, compared to the more dominant approach of proceeding in step-wise fashion (beginning with clinical efficacy, then clinical effectiveness and finally implementation research). Third, our study is designed to be rich in information, providing a considerable amount of data covering a range of outcomes (e.g., self-care, mental health, self-efficacy, strain, collaboration) for multiple stakeholders (e.g., clients, family caregivers, health care providers). Fourth, we have chosen objective measures for the outcomes examined, using well-established and validated instruments. Finally, our study involves multiple sites and jurisdictions, which will enhance the generalizability of the study’s findings.

There are some challenges that should also be acknowledged. The study is examining the immediate 6-month effects of the program, which represents the early stages of implementation. While this timeframe was sufficient to demonstrate the feasibility and potential effectiveness in the pilot study [43], it limits our ability to comment on the long-term sustainability of the program. We will not be able to forecast long-term behavioral change in clients, nor will we be able to comment on the program’s sustainability within the partner organizations after the study concludes. During the interviews and focus groups, we will ask interventionists about their intentions to gain insight into the potential for sustainability. Notably, the community partners who participated in the pilot demonstrated “buy-in” and a commitment to ongoing planning, implementation, and evaluation of the program [43]. Adoption and implementation has the potential to be high given that the program involves the combination of diabetes expertise and increased accessibility because it is community-based.

Self-management interventions are also recognized to be challenging to implement when they are delivered in diverse community-based settings and feature a plan of care that is individualized, sustainable, and targeted to a complex population. The program is reliant on having resources available within the community, and smaller or rural regions might not have the sufficient infrastructure to offer the program (or all aspects of it). It can also be difficult to reach community-dwelling older adults with T2DM and MCC. Recruiting targets typically set for younger demographics may not be realistic for this population [94]. Retention may also be difficult; researchers have reported high attrition rates in older populations [95, 96]. In an effort to address these challenges, the study team will strengthen training and communication with RAs. By using these mechanisms, recruitment can be improved because interviewers will be trained to build rapport and trust, while they also rely on clear guidelines for participant contact, flexible interview schedules that accommodate client preferences and information that appropriately orients participants to research including its procedures, risks, and benefits. Importantly, participants will be given adequate time to decide whether to participate. Similarly, retention will be enhanced because interventionists will be guided to maintain regular and personalized contact with participants for the duration of the study. The research team will also facilitate retention by mailing reminder letters at 2 months and having the RA make a reminder phone call at 4 months. The researchers will also meet regularly with the interventionists to proactively address any issues related to the delivery of the program.

Finally, we have designed the program to be delivered in two different jurisdictions and multiple sites. The strength of this approach is that it will increase the generalizability of the results, potentially improve the uptake of results in new communities, and speed the translation of research into practice. However, involving multiple sites also introduces certain challenges. As this is a pragmatic trial, we both expect and encourage interventionists to make adaptations to address their local context and client needs. The risk is that these adaptations may lead to variability in the program’s delivery, particularly in component features and dose. Close monitoring will help the investigators to evaluate fidelity, or the consistency with which the components were applied, as well as the dose of the intervention actually delivered [97]. We will examine the impact of this variation on outcomes, similar to a dose-response analysis and address this in our findings [97, 98]. We will track any adaptations that are made to the program during its implementation. This information will be used to guide future refinements and prepare for a future study to test the program on a larger scale.

Ultimately, the study results will inform policy concerning community-based interventions to enhance self-management of T2DM. The study includes outcomes for a range of stakeholders (clients, family caregivers, health care providers) and includes a cost analysis. It will inform both clients and health care providers and improve our understanding of the effectiveness of group-based interventions in changing self-management behaviors in a complex and underserved population (older adults with T2DM and MCC). By including the evaluation of both effectiveness and implementation in one study design, we hope to enhance the relevance and sustainability of the study results to clinicians and policy-makers, and reduce the research-practice gap.

